#### Longitudinal stability of baseline subgroups and subgroup transitions

Within- and across-data type clustering will be performed independently at multiple time points and evaluate the frequencies of individual-level membership transitions. This aim is similar in nature to clustering approaches used by P1 (H1d and H1e). However, the methods are adapted to account for the increased diversity and dimensionality of input data that will be used to identify latent subgroups. In P1, latent profile analysis and then latent growth curve modelling will be used to identify clusters of participants, and to determine if individual trajectories of substance use and functional outcomes are predicted by baseline EFs, respectively. P7 will extend the foundational work of P1 by examining patient trajectories based on data collected across projects 1-6 and determined using different, network-based methodologies. Critically, we will also identify socio-demographic, educational, and life experiential factors determining inconsistency in group membership over time. Subtypes based on integrative data analyses will be evaluated against more traditional clinical subtypes (such as those from P1) to determine if distributions of key demographics and outcomes are modified by the inclusion of multi-disciplinary input features.

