### Methods and planned analyses

#### Design and participants

The CDiA Program aims to recruit a total sample of 400 adults seeking treatment for AUD and/or SUD to participate in this observational, longitudinal study involving clinical and cognitive assessments at baseline and at a one-year follow-up period (see **Table 1** for a comprehensive list of clinical and cognitive assessments and the time points of each assessment). Inclusion criteria are: (1) 18 - 60 years of age; (2) meeting diagnostic criteria for a current (past year) AUD and/or SUD (not counting nicotine- or caffeine-related disorders); and (3) seeking support for substance use concerns. Exclusion criteria include: (1) acute intoxication or withdrawal; (2) active psychosis; (3) acute suicidality; and (4) history of severe head injury, dementia, severe neurodevelopmental disorders, and other medical conditions or medications that could severely impair cognition.

**Table 1 T1:** Schedule of clinical & cognitive assessments.

Procedure	Construct Measured	Baseline ^a^	Follow up ^b^	Year End ^c^
Informed Consent	N/A	✓		
Verbal confirmation of 12-hour abstinence and time of last substance use	Substance Use	✓		✓
Urinalysis and Breathalyzer	Substance Use	✓		✓
Performance-Based Measures				
CNS-Vitals ^¢ θ^	Cognitive Functioning: General	✓		✓
Iowa Gambling Task ^¢ θ^	Cognitive Functioning: Decision Making	✓		✓
Delay Discounting Task ^¢^	Cognitive Functioning: Decision Making	✓		✓
Probability Discounting Task ^¢^	Cognitive Functioning: Decision Making	✓		✓
Flanker Task ^¢ θ^	Executive Functioning: Inhibitory Control	✓		✓
N-back Task ^¢ θ^	Executive Functioning: Updating	✓		✓
Switch Task ^¢ θ^	Executive Functioning: Set Shifting	✓		✓
Interview-Based Measures				
Diagnostic Assessment Research Tool (55)^d^	AUD, SUD, and other mental health diagnoses	✓		✓
Timeline Follow Back (56)	Substance Use	✓		✓
Psychiatric Treatment History	Treatment History: Medications	✓		✓
Psychological Treatment	Treatment History: Psychological	✓		✓
Self-Report Measures				
Demographics ^$^	Identity	✓		
Bem Sex Role Inventory (Short Form) (68, 69) ^$^	Identity	✓		
Lifetime substance use history (70) ^$^	Substance Use	✓		
Alcohol Use Disorders Identification Test (71) ^$^	Substance Use and Harms	✓		✓
Drug Use Disorders Identification Test (72) ^$^	Substance Use and Harms	✓		✓
Fagerström Test for Nicotine Dependence (73) ^$^	Substance Use and Harms	✓		✓

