### Methods and planned analyses

#### Participants

All participants included in the total sample are invited to participate in a 1.5-hour MRI protocol. P2-specific exclusion criteria include the presence of MRI-incompatible metal implants, history of stroke, and claustrophobia. We anticipate approximately 50% of the entire sample (n=200) will be eligible and consent to MRI. Eligible participants are invited for a longitudinal scan at one-year follow-up; we anticipate 25% (n=50) being available and consenting to the repeat scan to assess longitudinal stability of our main measures. Given the specific safety requirements of MRI, it is possible that the final P2 sample will not be fully representative of the P1 sample in terms of demographics and clinical characteristics. If this is the case, we will consider this important caveat in interpreting any results using joint P1-P2 and conduct sensitivity analyses where appropriate.

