#### H2

Subtypes from Aim 1 will be predictive of changes in EF over one year of follow-up and individuals with evidence for subgroup transition will experience different treatment response rates.

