### Methods and planned analyses

#### Cross-sectional data-driven subtyping

This will involve using subject clustering algorithms to identify relatively homogeneous subgroups of patients. Primary measurements from each of P1-6 will be used as input for clustering (see **Table 4** for domain definitions). The similarity network fusion (SNF) method will then be used to combine more fine-detailed, high-dimensional input variables across multiple modalities. To address the key overarching theme of this proposal, subgroups based on EF domains (including and excluding other measures, as in P1 objectives) will be of particular interest, and will be tested for distributional differences in primary prognostic outcomes of functional recovery and sustained health. The semi-supervised association-boosted SNF (abSNF) method will be used to identify subgroups with most significance to EF performance at baseline. Internal validation of group membership will be performed using bootstrap procedures. Socio-demographic, educational, and life experiential characteristics of each subgroup will be described and placed within the context of existing cross-sectional work.

**Table 4 T4:** Summary of assessment domains and measurements across study projects.

Project	Domain (instrument/source)	Measures
1	Clinical (DART, suicidal ideation) + Substance use (TFLB, AUDIT, DUDIT, SDS)	Psychiatric diagnoses, comorbidity, suicidal ideation, childhood adversity, medication, treatment engagement
		Recent and lifetime history of (poly)substance use
		Age of onset, average yearly use, heaviest period of use
	Cognition (CNS-VS, executive function tasks, other behavioral tasks)	Global cognitive function
		Executive function (Inhibition, updating, set shifting) deficits and biases
		Risk and reward behavior
	Functional impairment and quality of life (WHOQOL-BREF, WHODAS)	Physical, psychological, social, and environmental
		Cognition, mobility, self-care, getting along, life activities, and participation
2	Neuroimaging (3T MRI)	Task-based and resting state fMRI
		T1-weighted structural MRI
		Neuromelanin-sensitive MRI of SN/VTA and LC
		Diffusion MRI
3	Genomics	Assay-based genome-wide genotypes
		Assay-based genome-wide methylation profiles
	Plasma biomarkers	Inflammasome proteins (NF-KB, ERK, and p38MAPK, NALP3)
		Pro-inflammatory cytokines (IL-1β, IL-18, and ProCaspase-1)
4	Intervention (4 week TMS) clinical outcomes	Suicidal ideation (SSI)
		Depressive symptoms (HRSD-17)

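### Project 7 counts membership changes between independently fitted cluster solutions as transitions, with no reference for how many would appear if nobody changed

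*Protocol article*

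**What the plan says.** The longitudinal part of Project 7 (section *Longitudinal stability of baseline subgroups and subgroup transitions*) states that "clustering will be performed independently at multiple time points and evaluate the frequencies of individual-level membership transitions". Two analyses use the result as a characteristic of the person:

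- Project 7, H2, expects that "individuals with evidence for subgroup transition will experience different treatment response rates".
- The longitudinal section adds that "we will also identify socio-demographic, educational, and life experiential factors determining inconsistency in group membership over time".

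The only stated stability check is under *Cross-sectional data-driven subtyping*: "Internal validation of group membership will be performed using bootstrap procedures". It is not tied to the transition counts. The same section names the method: "The similarity network fusion (SNF) method will then be used to combine more fine-detailed, high-dimensional input variables across multiple modalities", with a semi-supervised variant directed at executive function (EF).

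On the available data, Project 1 says "The CDiA Program aims to recruit a total sample of 400 adults seeking treatment for AUD and/or SUD". Project 2 says "We anticipate approximately 50% of the entire sample (n=200) will be eligible and consent to MRI" and, for the one-year scan, "we anticipate 25% (n=50) being available and consenting to the repeat scan to assess longitudinal stability of our main measures". Table 1 gives the EF tasks at baseline and year end only. At months 2 to 10 it repeats only the dependence severity, disability and quality-of-life scales. Lifetime substance use history and the childhood trauma questionnaire are taken at baseline only, although Table 4 lists both constructs among the Project 7 domains.

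**The concern.** When clustering is run afresh at each visit, the boundaries between clusters are estimated afresh too. A participant near a boundary can change cluster because the boundary moved or because the second measurement carried different error, with no change in the person. The plan counts all such moves together with real ones.

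This would matter little if the count only described how reproducible the clusters are. Here the moves become a variable in two further analyses. If many are spurious, the H2 contrast in treatment response compares groups that are largely mixed. The search for determinants of inconsistency may then pick out characteristics that go with noisier measurement or with lying near a boundary.

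Differing inputs add to this. A solution that uses a feature or a scan at one visit and not at the other can move people because the data changed.

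**Working it through.** **The plan's own figures.** The article states no expected transition rate, number of clusters or power for this analysis, so there is no figure to reproduce. The imaging arithmetic is consistent: 50% of 400 = 200, and 25% of 200 = 50. About 150 of the 200 scanned at baseline would therefore have no repeat scan.

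**Question.** If nobody changes, what share is counted as having moved?

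**Inputs.**
- From the article: n = 400 (cohort) and n = 50 (repeat scans).
- Assumed: k = 3 or 5 clusters; 6 features; centres 0, 2 or 4 within-cluster SD apart (root mean square distance between centres); reliability r = 0.7, 0.9 or 1.0.
- K-means with 10 starts stands in for similarity network fusion. There are 60 replicates per setting.

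**Model.** Each person has one stable score vector, equal to cluster centre plus unit-variance within-cluster variation. Each visit adds independent error with SD = √((1 − r)/r), which is 0.65 at r = 0.7, 0.33 at r = 0.9 and 0 at r = 1.0. True transitions are zero by construction.

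**Two ways of counting.** (a) Cluster each visit independently and match clusters across visits by optimal assignment. (b) Cluster baseline only and assign follow-up data to the nearest baseline centre.

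**Results, n = 400, k = 3.**

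| Separation (SD) | r | (a) independent, matched | (b) baseline fixed | (a) − (b), points |
|---|---|---|---|---|
| 0 | 0.7 | 49.8% | 32.7% | 17.1 |
| 0 | 0.9 | 40.5% | 17.6% | 22.9 |
| 0 | 1.0 | 27.2% | 0.8% | 26.4 |
| 2 | 0.7 | 34.9% | 27.0% | 7.9 |
| 2 | 0.9 | 21.4% | 14.4% | 7.0 |
| 2 | 1.0 | 6.4% | 0.3% | 6.1 |
| 4 | 0.7 | 12.7% | 11.9% | 0.8 |
| 4 | 0.9 | 6.3% | 5.7% | 0.6 |
| 4 | 1.0 | 0.2% | 0.0% | 0.2 |

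At r = 0.9, method (a) labels 0.405 × 400 = 162 people as moved with no clusters, 0.214 × 400 = 86 with moderate clusters and 0.063 × 400 = 25 with clear ones. At r = 1.0 the data are identical at both visits, so the figures under (a) come from the clustering procedure alone.

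With k = 5 (r = 0.9 to 0.7), (a) gives 51% to 61%, 41% to 54% and 12% to 25% at 0, 2 and 4 SD. With n = 50, k = 3 and 2 SD, it gives 26% to 40%.

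Repeat runs at n = 400 and k = 3 gave 39% to 49%, 16% to 31% and 4% to 11% at 0, 2 and 4 SD. Together with the table at r = 0.7 and 0.9, the ranges are 39% to 50%, 16% to 35% and 4% to 13%.

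**Where it comes from.** At 2 SD, the part that remains under (b) is 14.4/21.4 = 67% of the total at r = 0.9 and 27.0/34.9 = 77% at r = 0.7. At 4 SD it is at least 5.7/6.3 = 90%. Where clusters exist, most of the spurious movement is measurement error, which holding the baseline solution fixed does not remove. Where none exist, re-estimation accounts for a large part.

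**The case against.** Much can be said for the plan.

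- The section heading speaks of stability, the Project 7 background criticises earlier subtyping for unstable results, and a bootstrap is planned. The authors know that clusters can be unstable. Independent re-clustering is a sound way to ask whether the same structure recurs. This stands, but it does not cover the use of individual moves as a variable in H2 and in the inconsistency analysis.
- H2 leaves open what counts as evidence for a transition, and the full protocol or analysis plan may define it. That is fair. What the article does fix is independent solutions and a count of individual moves, and nothing in it separates those moves from noise.
- The percentages rest on assumed parameters and a simpler clustering method. This stands. With clear clusters and reliable measures the problem is small.
- Carrying the baseline solution forward is no clean cure. Project 1 (H1e) expects EF to improve over the year, and practice effects are possible. With severity-ordered clusters 1 to 2 SD apart, reliability 0.7 to 0.8 and a uniform shift of 0.3 SD, the fixed baseline gave 19% to 34% apparent transitions against 8% to 32% for independent clustering with matched labels. With differently shaped profiles the shift mattered little. This stands and shapes the fix.

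A reader might also infer that arbitrary cluster labels will be compared as output, so that relabelling alone creates transitions. The article does not say so. Matching clusters across visits is a routine step that an article may leave out, and every figure used here assumes it is done.

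**Conclusion.** The concern holds in a limited form. As written, the plan counts cluster instability and measurement error as transitions and gives no rate expected under no change. Under the stated assumptions the spurious share after matching is roughly 4% to 13% with clear clusters, 16% to 35% with moderate ones and 39% to 50% with none (n = 400, k = 3, reliability 0.7 to 0.9). It is larger with five clusters. Real separation and reliability are unknown, so these are not predictions for this cohort.

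Three stronger readings are not supported. The documents do not show that many false transitions will certainly be reported, because that depends on separation. They do not show that the H2 association will be created falsely, because purely random misclassification would usually weaken it. Nor is Project 7 undermined as a whole: the limb of H2 in which baseline subtypes predict EF change does not use transitions. The effect is confined to the transition limb of H2 and the inconsistency analysis, and the Project 4 comparison of active with sham stimulation is untouched.

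**What to change.** Before testing the transition limb of H2 or seeking determinants of inconsistency:

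1. Restrict transition analyses to features and participants measured at both time points. For EF this means baseline and year end. For imaging it means those with repeat scans.
2. Compare observed transitions with a no-change reference, for example a parametric bootstrap at the measures' retest reliability, extending the bootstrap already planned for the cross-sectional subtypes. Take only changes beyond that reference as evidence of transition, or weight people by the uncertainty of their membership.
3. Add, as main or sensitivity analysis, either follow-up data assigned to the baseline solution or a joint or latent-transition model. Keep independent clustering to check whether the structure recurs.

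No new data are needed. The costs are more analysis work and fewer people in imaging-based transition analyses. Fixed definitions can miss clusters that first appear at follow-up, and can register a uniform cohort shift or practice effect as transitions. That is why they should stand beside independent clustering and not replace it.

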#### Supervised machine learning for prognostication

We will apply machine learning methods on features identified by each project across domains to build optimally predictive models of: (1) EF, (2) social function, (3) suicidality and self-harm, and (4) healthcare system burden (234). Modelling will proceed iteratively, using processes developed by our group (235–237).

## Discussion

There is widespread recognition of the need for integrative and longitudinal research incorporating cognitive, biological, and clinical measures of vulnerability and resilience in SUDs. Within the CDiA Program structure, detailed clinical and cognitive characteristics of a treatment-seeking sample will be integrated with biological markers closely linked to both cognitive dysfunction and SUDs, permitting the identification of critical mechanisms and therapeutic targets. Linkages to healthcare utilization and innovative whole-person modeling approaches will further take this initiative from “neuron-to-neighborhood” and foster integrative and translational research consistent with recent calls to action in this field.

A main strength and innovation of the CDiA Program consists of its translational team and unique collaborative research approach on executive dysfunction for functional recovery and sustained health in outpatients seeking treatment for SUDs (**Figure 1**). Other conceptual advantages of the Program are the adoption of an individual differences approach, appreciation for patient complexity and heterogeneity, and the recognition that transformation of care can only occur when combining expertise from clinical neuroscience, clinical care, clinical research, and epidemiology/health science research perspectives. As depicted in **Figure 1**, P1-4 are closely linked investigations with a focus on collecting deep data in complex patients seeking treatment for SUDs; these human subjects research projects emphasize ecological validity and will occur in parallel with Project 5, which offers the opportunity to investigate associations between EFs, proposed biological underpinnings, and associated pharmacological therapeutics in a highly controlled and efficient design. P6 and P7 extend the generativity of this work, with a focus on healthcare utilization and costs, as well as lived experience perspectives, and the application of highly sophisticated, advanced computational modeling to integrate data across all other projects. To further demonstrate the intended integrated approach across projects, we provide here selected examples of potential for individual projects benefiting and feeding back on strategy, approach and deliverables of other projects (see **Table 5**).

**Table 5 T5:** Cross-Disciplinary collaboration across projects.

Clinical and cognitive measures collected within P1 will be linked to neuroimaging biomarkers collected within P2, peripheral biomarkers collected within P3, and healthcare utilization and costs indexed in P6.
Clinical and cognitive measures collected within P1 will further characterize participants with elevated suicidality who receive rTMS as part of P4, and contribute to the whole person modeling planned for P7.
Executive function tasks included in both P1 and P5 were carefully chosen to ensure consistency with current models of executive function and with each other. P1 will also track pharmacological treatments, and exploratory analyses of the effects of naltrexone on executive functioning in P1 will be informed by P5 preclinical models of the effects of naltrexone and other medications on executive functioning.
Neuroimaging measures collected within P2 will be mapped onto peripheral molecular markers assessed in P3
The dopamine and norepinephrine systems, whose integrity will be indexed with NM-MRI, are conserved across species and can be manipulated in preclinical models, hence creating opportunities for collaboration between P2 and P5
Innovative therapeutic approaches targeting key mechanisms involved in AUDs and executive dysfunction, such as GABAergic deficits (P4) and inflammasome activation (P3), will be tested to characterize their efficacy at reducing domains of alcohol-related executive dysfunction in P5.
P5 will provide an experimental assay for AUD-related executive dysfunction and a repository of biological samples for future proof-of-concept studies aimed at novel biological pathways discovered in this project (i.e. P4)
Both P4 and P5 target the GABA system, permitting the evaluation of innovative treatment alternatives that may show promise in those with alcohol use difficulties and associated cognitive dysfunction
P5 targets the inflammasome using innovative compounds as well and will synergize with P3 biomarker studies and P7 integration studies
The clinical, imaging, and peripheral markers within P1, P2 and P3 can be utilized to predict health care utilization and the costs of this utilization within P6
P6 will investigate which of the associations of executive function deficits with SUD treatment experiences and healthcare utilization differ across those with and without pervasive suicidality, and thus will inform and be informed by P4
P6 will investigate whether the associations of executive function deficits and health care utilization and costs differ among those who used naltrexone versus those who did not, and will thus inform and be informed by P5
P7 is the end-cap of the analytical pipeline for the proposed study and the key point of integration across preceding projects. Knowledge generated in P1-6 will be essential for determining which of the measured variables across domains will be most informative in statistical modeling.

Our inclusive approach to participant recruitment will allow us to recruit a large sample representative of the complex clinical populations typically seen in tertiary care settings. We recognize this will also pose analytical challenges related to sample heterogeneity. Our reliance on multi-level measures of transdiagnostic relevance (e.g., EF, functioning, neural circuit function, inflammatory markers) and our state-of-the-art data integrative approaches outlined in P7 place the CDiA Program in a strong position to harness this heterogeneity to improve understanding of “real-world” presentations of SUDs and their cognitive features. This can in turn accelerate impactful discovery science, clinical translation, and societal/policy changes needed to improve outcomes in this population.

It is anticipated that following the recruitment of this initial cohort, subsequent research will investigate the impact of specific interventions (20, 238) on impaired EFs and functional outcomes. Thus, it is the vision to use these results to support an “experimental medicine” approach aimed at remediating cognitive dysfunction. Peripheral and imaging biomarkers identified in our initial cohort will permit such a nuanced investigation of mediators of clinical outcomes, and in conjunction with preclinical investigations, will inform the development of novel therapeutics (239, 240). Although both psychosocial (e.g., cognitive training) and biological (e.g., pharmacotherapy, noninvasive brain stimulation) interventions are forecasted, the first planned intervention will investigate the efficacy of rTMS on outcomes in SUDs. However, participants in the broader CDiA program are expected to be enrolled in a variety of treatment programs across CAMH and beyond. Thus, although Projects 1-3 of the broader CDiA Program are not centered on a specific clinical trial, they are well-positioned to capture symptom changes and recovery across a variety of therapeutic contexts over time. Given the intended generativity of the program, we do anticipate that the current work will give rise to new, larger and potentially more comprehensive treatment trials directed by initial insight from CDiA.

